## Methods

### Design

We will conduct a 12-month, parallel group, proof-of-concept RCT of 88 community-dwelling adults with SIVCI, aged 55 years and older. Participants will be randomly assigned to receive 12 months of (1) twice-weekly PRT or (2) twice-weekly balance and tone training (BAT; active control). There will be three measurement points occurring at baseline, 6 months, and 12 months conducted by blinded assessors (Fig. 1). The experienced research team will implement standardized protocols and train study personnel (Fig. 2).

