### Sample size calculation

Power analyses were conducted in G*Power 3.1 [48]. We have sized this trial to allow the evaluation of PRT on the Alzheimer's Disease Assessment Scale-Cognitive-Plus (ADAS-Cog-Plus) [49] and WMH progression at trial completion; WMH progression is considered a valid surrogate marker in therapeutic trials of SIVCI [50]. The ADAS-Cog-Plus is the original ADAS-Cog-13 with additional measures of executive functions and verbal fluency, and it is more sensitive to subtle cognitive changes than the original ADAS-Cog-13 or ADAS-Cog-11 [49]. Our prior 6-month RCT of aerobic exercise on cognitive function, as measured by the ADAS-Cog-11, in adults with SIVCI observed an effect size of 0.89 (Cohen’s *d*) in the complete-case analysis [51]. We also demonstrated twice-weekly PRT slowed WMH progression in older women; the effect size observed was 0.60 (Cohen’s *d*). Based on this effect size of 0.60, assuming an alpha of 0.05 (two-tailed) and a beta of 0.20, 35 participants per group will provide a power of 0.80 [48]. We are aiming to recruit a total of 88 participants with SIVCI (i.e., 44 participants per group), which will accommodate a conservative 20% drop-out rate.

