##### White matter hyperintensity quantification

Brain MRI scans will be acquired at baseline and trial completion (12 months) at the UBC MRI Research Center. Neuroimaging will be performed on a Philips 3.0-Tesla Achieva scanner (Best, The Netherlands) with an 8-channel phased array head coil. Three-dimensional (3D) T_2_-weighted (T_2_-w) and proton density-weighted (PD-w) structural MRI scans will be acquired to quantify WMH volume.

For detailed information on MRI sequence parameters, please refer to Table 1.

**Table 1 Tab1:** Magnetic resonance imaging protocol

	3D T_1_-w MPRAGE^a^	3D T_2_-w	PD-w	DWI^b^	GRASE	rs-fMRI
Resolution acquired/reconstructed (mm^2^)	1 × 1/1 × 1	1 × 1/0.8 × 0.8	0.99 × 1/0.98 × 0.98	2.24 × 2.24/2 × 2	0.99 × 2.04/0.96 × 0.95	3 × 3/3 × 3
Slice thickness acquired/reconstructed (mm)	1/1	1.6/0.8	1/1	2.20/2.20	5/2.5	3/3
Number of reconstructed slices	170	200	170	70	40	36
Field of view ap/rl/fh (mm)	256 × 200 × 170	256 × 160 × 256	250 × 170 × 250	224 × 224 × 154	230 × 190 × 100	240 × 240 × 143
Orientation	Transverse	Sagittal	Sagittal	Transverse	Transverse	Transverse
Echo time (ms)	3.5	363	30	60	8, 16, 24 … 384	30
Repetition time (ms)	1800	2500	3000	7.1	1073	2000
Flip angle (deg)	8	90	90	90	90	90
Acquisition time (min)	6:34	4:43	10:33	7:27	7:30	5:00
Purpose	Anatomical reference	WMH quantification	WMH quantification	White matter integrity quantification	Myelin quantification	Functional connectivity assessment

*ap* anterior-posterior, *rl* right left, *fh* foot-head

^a^Additional sequence parameters for 3D T_1_-w MPRAGE: inversion time = 810 ms

^b^Additional sequence parameters for DWI: 60 gradient directions at *b* = 700 s/mm^2^, 1 unweighted scan

T_2_-w and PD-w images will be preprocessed using standard and publicly available neuroimaging tools that include: (1) MR intensity inhomogeneity correction using a multiscale version of the nonparametric non-uniform intensity normalization method (N3) [58]; (2) a structure-preserving noise-removal filter (SUSAN) [59]; and (3) all non-brain tissues will be removed using the brain extraction tool (BET) [60].

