### Statistical analyses

The analyses will follow the intention-to-treat principle (i.e., all individuals will be analyzed according to their group allocation regardless of compliance). We will evaluate between-group differences (PRT vs. BAT) in ADAS-Cog-Plus and WMH volume, adjusted for baseline score, using mixed linear models. Restricted maximum likelihood estimation will be used in order to include all randomized participants to estimate treatment effects, regardless of loss to follow-up. Time since baseline (6 months versus 12 months) will be considered as a repeated variable and will be included as a fixed effect in addition to group and group-by-time interaction. Baseline score on the outcome variable and participant baseline characteristics will be included as fixed covariates. The intercept will be specified as a random effect. Primary and secondary outcomes will be analyzed using this same analytic model.

The intention-to-treat analysis will be followed by a complete-case analysis, in which only participants with valid data at all time points will be included. Moreover, we will compare participants in the PRT group who are compliant with the intervention (defined as attending at least 60% of the total exercise sessions) with the BAT group.

To explore underlying mechanisms, we will assess the association between changes in cognitive function with changes in: (1) neuroimaging outcomes; (2) cardiometabolic risk factors; (3) blood biomarkers; and (4) saliva biomarkers.

The economic evaluation will examine the efficiency of the 12-month PRT program compared with BAT. The outcome of our cost–utility analysis is the incremental cost–utility ratio (ICUR): ICUR = ∆Cost/∆ quality-adjusted life years (QALYs); QALYs, estimated from the EQ-5D-5L, represent time spent in given health states [85, 86].

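### For outcomes measured at 6 and 12 months, the stated random intercept, on its usual reading, gives both visits one variance and can miscalibrate the 12-month contrast; for WMH the same model cannot be identified

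*Protocol article*

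**What the plan says.** The Statistical analyses section adjusts for baseline and sets out the model in a few sentences:

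- Repeated factor: "Time since baseline (6 months versus 12 months) will be considered as a repeated variable".
- Fixed effects: time "will be included as a fixed effect in addition to group and group-by-time interaction", plus the baseline score and baseline characteristics.
- Within-person structure: "The intercept will be specified as a random effect". No random slope, visit-specific variance or residual covariance type is named.
- Scope: "Primary and secondary outcomes will be analyzed using this same analytic model".

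Two other sections bear on it. The Sample size calculation sizes the trial for ADAS-Cog-Plus and for "WMH progression at trial completion", so 12 months is the time point of interest. The Design section says "There will be three measurement points occurring at baseline, 6 months, and 12 months", but the section on WMH quantification gives imaging only two occasions: "Brain MRI scans will be acquired at baseline and trial completion (12 months".

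**The concern.** A random intercept with independent, equal-variance residuals is compound symmetry: one variance for both follow-up visits and one covariance between them. The standard error of the 12-month group difference then rests on a pooled variance, not on the variance at 12 months. If people are more spread out at 12 months than at 6, given baseline, the interval is too narrow. If they are less spread out, it is too wide.

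This matters most for ADAS-Cog-Plus. It is a primary outcome, the trial is sized for its value at trial completion, and the Primary outcomes section accepts improvement in either primary outcome as evidence of efficacy. An inflated error rate on the 12-month cognitive contrast would therefore pass straight into the trial's claim.

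WMH has a different problem. With a single follow-up value, a model built on a 6-versus-12-month factor and a random intercept cannot be fitted as described.

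**Working it through.** The article gives no variance by visit, no within-person correlation and no covariance type, so it contains no figure on this point to reproduce. The check asks how far the error rate moves over a range of assumed SD ratios.

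**Inputs from the article:** 44 per group, 1:1 allocation, 20% drop-out, two-tailed alpha 0.05, visits at 6 and 12 months, adjustment for baseline.

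**Assumed:** k, the ratio of the 12-month to the 6-month SD after baseline adjustment.

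**Analytic step (complete data, homogeneous residuals).** The model bases the 12-month variance on (s6² + s12²)/2, where the truth is s12². Hence

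model SE / true SE = sqrt((1 + k²) / (2k²)), and actual alpha = 2 × (1 − Φ(1.96 × ratio)).

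For k = 1.2: sqrt(2.44 / 2.88) = 0.920; 1.96 × 0.920 = 1.804; alpha = 0.071.

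| k | model SE / true SE | actual two-sided alpha |
|---|---|---|
| 0.8 | 1.13 | 0.027 |
| 1.0 | 1.00 | 0.050 |
| 1.1 | 0.96 | 0.061 |
| 1.2 | 0.92 | 0.071 |
| 1.5 | 0.85 | 0.096 |

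**Simulation (REML, 44 per group, 20% missing at 12 months, within-person correlation 0.6).** Type I error of the 12-month contrast:

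| k | random intercept, homogeneous residuals | unstructured |
|---|---|---|
| 1.0 | 0.051 | 0.052 |
| 1.2 | 0.079 | 0.049 |
| 1.5 | 0.101 | 0.053 |

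A second simulation, with correlation 0.5, 20% loss and 1,200 runs per setting (simulation error about 0.006), gave 0.048, 0.076 and 0.114 for the random intercept at k = 1.1, 1.25 and 1.5. So at k = 1.1 the effect is within simulation noise, and it becomes clear from about k = 1.2.

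**Why k might exceed 1.** The relevant spread is what remains after baseline. If the total SD is constant but baseline correlates 0.80 with the 6-month score and 0.70 with the 12-month score (assumed values), then k = sqrt((1 − 0.49) / (1 − 0.64)) = 1.19, and alpha is about 0.070. This shows how k could rise; it does not show that it does.

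**Power cost of the alternative.** With equal SDs and d = 0.60, simulated power was 0.753 for the random intercept and 0.750 for unstructured covariance. With 600 runs the simulation error is sqrt(0.75 × 0.25 / 600) = 0.018, so no difference is detectable.

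**WMH.** With one post-baseline value per person, time has a single level, so the time and group-by-time terms drop out. The intercept variance and the residual variance enter the likelihood only as their sum and cannot be estimated separately. The group effect remains estimable and is the ANCOVA estimate.

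**The case against.** The strongest reply is that the article does not fix the residual covariance at all. It names time as a repeated variable as well as a random intercept, and never says that residual variances are equal. A random intercept with visit-specific residual variances has three parameters for two visits and, with positive within-person correlation, is the unstructured matrix. Covariance type and degrees-of-freedom method are also details that a condensed article may leave to a fuller document, which is not shown here. This stands. A reader might infer that the plan forces equal variances or uses a random intercept alone, and the text does not support that. The silence is not itself an error. The point is that the one structure the article does name has a default reading that is open to miscalibration.

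The second reply is that growing spread is conjecture. That also stands: the article gives no SD by visit, and at a ratio of 0.8 the same model is conservative. A reader might infer that standard errors will be too small, but only miscalibration in an unknown direction can be claimed.

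The third reply is that the variance argument cannot reach WMH or the other MRI outcomes, which have one follow-up scan. This is correct. It is also fair that the stated model collapses there to a baseline-adjusted comparison, so the WMH group estimate itself is not biased by the wording.

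**Conclusion.** The point holds in limited form, with medium confidence. It concerns ADAS-Cog-Plus and the non-imaging secondary outcomes measured at both visits, and it depends on the usual reading of a random intercept with homogeneous residuals. On that reading, nominal 0.05 becomes roughly 0.06 to 0.10 for SD ratios of 1.1 to 1.5, falls to 0.027 at 0.8, and is correct at 1.0. These figures rest on an assumed ratio and, analytically, on complete data; the simulations with 20% loss agree in direction and rough size.

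For WMH and the other imaging outcomes there is no variance pooling and no inflation to claim. What remains is that the shared model cannot be identified as written for an outcome with a single follow-up.

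This is not evidence that the trial's inference is invalid. It is a recommended clarification that removes a moderate risk at almost no cost.

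**What to change.** In the Statistical analyses section, or in the analysis plan before unblinding:

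1. For ADAS-Cog-Plus and other outcomes measured at 6 and 12 months, replace the random intercept with an unstructured within-person covariance (three parameters) and use Kenward-Roger degrees of freedom.
2. State that the group difference at 12 months is the primary contrast, in line with the sizing at trial completion.
3. For WMH volume and the other MRI outcomes, specify ANCOVA of the 12-month value on baseline and group, keeping any planned baseline covariates, and exempt them from the shared-model sentence.

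A baseline-by-time term is optional; the variance argument does not require it.

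The cost is a few words. No extra data are needed, and power was 0.750 against 0.753 when the variances are equal. For WMH, ANCOVA loses nothing against the stated model, because a participant without a 12-month scan contributes no outcome value under either.

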##### Allocation concealment

Participant recruitment and enrollment will be managed by research personnel who will screen for eligibility, acquire consent, and conduct baseline assessments. Randomization to an intervention group will occur after completion of the baseline assessments. Research personnel conducting assessments and data analysis will be blinded to group allocation so unblinding will not occur. We will not be able to blind participants or personnel delivering the interventions and obtaining the monthly physical activity data (see intervention compliance). Blinding will be supported by providing explicit instructions to the research personnel and participants not to discuss issues related to physical activity during the assessments.

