#### Intervention compliance

Class attendance will be recorded by the instructors and compliance will be defined as the percentage of the total classes attended. To promote adherence to the exercise program, we will implement strategies including: (1) regular contact; (2) developing coping and action plans; (3) setting implementation intentions and concrete plans; and (4) encouraging participants to self-monitor their progress. Monthly monitoring of extracurricular physical activities will also be performed by an unblinded assessor using the Physical Activities for the Elderly [83, 84] questionnaire throughout the study. In addition, at each measurement point, physical activity over 14 days will be quantified using data acquired by the MW8 [76].

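### The supplementary compliance analysis applies the 60% attendance rule to PRT only and compares those attenders with all of BAT, so its estimate is biased in expectation, probably towards PRT

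*Protocol article*

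**What the plan says.** The Statistical analyses section puts intention-to-treat first: "all individuals will be analyzed according to their group allocation regardless of compliance". Then "The intention-to-treat analysis will be followed by a complete-case analysis". The compliance comparison comes last. It is a comparison of "participants in the PRT group who are compliant with the intervention (defined as attending at least 60% of the total exercise sessions) with the BAT" arm. No attendance condition is placed on BAT.

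Three other places bear on this:

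- **Intervention compliance:** "Class attendance will be recorded by the instructors and compliance will be defined as the percentage of the total classes attended". This is not limited to PRT.
- **Randomization:** both programmes run twice a week for 12 months, so the same threshold can be computed in either arm.
- **Balance and tone training:** BAT is there to control for travel to the training centres, social contact and lifestyle change that come with taking part.

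For the main model, "Baseline score on the outcome variable and participant baseline characteristics will be included as fixed covariates". The article does not say whether the compliance comparison uses the same adjustment.

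**The concern.** Attendance is observed after randomisation and may be related to prognosis. Participants have cognitive impairment (MoCA below 26). Those who keep up twice-weekly classes for a year are plausibly the healthier ones and those declining more slowly. Filtering on attendance in PRT alone removes that arm's poorer attenders and leaves BAT's in place. The two sides then differ in prognosis as well as in programme.

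They also differ in class contact. BAT is meant to match PRT on contact, but PRT members with at least 60% attendance would be set against a BAT group that includes people who rarely came.

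What is at stake is how this one contrast is read. Beside a null intention-to-treat result, an apparent benefit in compliant PRT participants could be taken as evidence that PRT works when it is attended, although part or all of the difference could come from selection.

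**Working it through.** **The plan's own figures.** The article gives no figure for this comparison. The Sample size calculation section supplies the size of the trial: 35 per group, and 35/(1 − 0.20) = 43.75, rounded to 44 per group and 88 in total, as stated. It also gives a planning effect of d = 0.60. I use 35 only as the number evaluable per arm.

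**Assumed inputs (not in the article).** Share of PRT participants meeting the rule, p: 50–90%. Correlation ρ between attendance and outcome, after baseline adjustment and with no treatment effect: 0.1–0.4.

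**Model.** Latent attendance and outcome are bivariate normal. A PRT participant is kept if attendance exceeds the cut k = z(1 − p). PRT has no effect. Then:

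- bias = ρ·m SD, where m = φ(k)/p;
- outcome variance among those kept: v = 1 − ρ²·m·(m − k);
- SE = √(v/n₁ + 1/35), where n₁ is 35p rounded;
- false-positive rate = 1 − Φ(1.96 − bias/SE) + Φ(−1.96 − bias/SE).

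**One case in full (p = 0.7, ρ = 0.3).** k = −0.524 and φ(k) = 0.348, so m = 0.348/0.7 = 0.497.

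- Bias = 0.3 × 0.497 = 0.149 SD. Against the planning effect this is 0.149/0.60 = 0.25.
- v = 1 − 0.09 × 0.497 × 1.021 = 0.954.
- SE = √(0.954/24 + 1/35) = 0.261, and bias/SE = 0.570.
- False-positive rate = 0.082 + 0.006 = 0.088.

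**Full range: bias in SD (false-positive rate).**

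| p | ρ = 0.1 | ρ = 0.2 | ρ = 0.3 | ρ = 0.4 |
|---|---|---|---|---|
| 50% | 0.080 (5.9%) | 0.160 (8.6%) | 0.239 (13.4%) | 0.319 (20.7%) |
| 60% | 0.064 (5.6%) | 0.129 (7.6%) | 0.193 (11.0%) | 0.258 (16.1%) |
| 70% | 0.050 (5.4%) | 0.099 (6.6%) | 0.149 (8.8%) | 0.199 (12.0%) |
| 80% | 0.035 (5.2%) | 0.070 (5.9%) | 0.105 (7.0%) | 0.140 (8.7%) |
| 90% | 0.019 (5.1%) | 0.039 (5.3%) | 0.058 (5.7%) | 0.078 (6.2%) |

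**If drop-outs are the poor attenders.** As an extreme, suppose the 20% lost in each arm are exactly the lowest attenders and contribute no follow-up. Evaluable BAT is then also selected, at the 80% cut where m = 0.350. With p the share of all 44 PRT participants, the bias becomes ρ·(m(p) − 0.350).

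- p = 0.8: bias is 0.
- p = 0.6, ρ = 0.4: bias is 0.4 × (0.644 − 0.350) = 0.118 SD. SE = √(0.908/26 + 0.933/35) = 0.248, giving a false-positive rate of about 7.6%.

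This case is too favourable to the plan, because the mixed model keeps participants with partial follow-up. It does show that the main table is not a lower limit.

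**The alternatives under no effect.** With the 60% rule in both arms the shift is ρ·m on each side and cancels, provided attendance relates to outcome alike in both. A complier-average estimate divides the intention-to-treat difference by the difference in exposure, so a true difference of zero stays zero.

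**The case against.** The strongest reply is that this is a late, supplementary contrast. Intention-to-treat comes first, and nothing in the article says efficacy will be judged on the compliance comparison. That stands. A reader might infer that the plan breaks the randomised comparison on both primary outcomes; the article does not support that, because only this contrast is non-randomised.

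A reader might also infer that the analysis would show a PRT benefit even if PRT did nothing. The figures do not support that either: with a false-positive rate of 5–21%, some 79–95% of null trials would still show no significant difference. The defensible statement is bias in expectation.

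The magnitude rests on assumed inputs, and this objection also stands:

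- Baseline adjustment, if used here, would lower the residual correlation, though it cannot remove unmeasured prognosis linked to attendance.
- The attendance argument fits ADAS-Cog-Plus better than WMH volume. The article gives no reason to expect the same correlation for WMH, and with zero correlation the bias is zero.
- The article does not state which SD underlies d = 0.60, so the ratio to 0.60 is only a guide.

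A further tempting reading is that the one-arm filter contradicts the blinding statement, "Research personnel conducting assessments and data analysis will be blinded to group allocation so unblinding will not occur". I would not press it. The arm can be disclosed once the intention-to-treat analysis is done, and a complier-average analysis based on PRT attendance also reveals which arm is PRT.

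Finally, labels and caveats may sit in a fuller document that is not shown, so their absence is not the point. The article itself fixes the threshold, the arm it applies to and the comparator. That asymmetry is what needs changing.

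**Conclusion.** The point holds for the supplementary compliance analysis only. As written, it conditions on post-randomisation attendance in PRT and not in BAT. Its estimate is therefore biased in expectation, probably in PRT's favour, and BAT no longer serves as a like-for-like control for class contact. The primary intention-to-treat inference is unaffected.

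Under the assumed ranges (50–90% compliance, residual correlation 0.1–0.4, about 35 evaluable per arm) the bias under no effect is about 0.02–0.32 SD and the false-positive rate about 5–21%. At 70% compliance and correlation 0.3 they are 0.15 SD and about 9%. Both shrink towards no bias and 5% if compliance is very high, if the correlation is weak, or if drop-outs in both arms are mostly poor attenders. The direction assumes that attenders have the better prognosis, which is plausible but not shown in the article.

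**What to change.** Keep intention-to-treat as the main analysis and change the compliance comparison in one of two ways.

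1. **Complier-average causal effect (preferred).** Keep all randomised participants, with allocation as the instrument and PRT attendance as the exposure. State the exclusion assumption. With the 60% cut, it is that allocation to PRT rather than BAT makes no difference to the outcome of those who attend less than 60%. With the proportion of sessions as exposure, it is that allocation acts only through sessions attended. The cost is a wider interval: with the 60% cut, about 1/p times the intention-to-treat width if sampling error in p is ignored, so 1/0.7 ≈ 1.4 times at 70% compliance. It adds little evidence against the null beyond intention-to-treat.

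2. **Symmetric rule.** Apply the 60% threshold to both arms, adjust for the outcome's baseline score and baseline predictors of attendance, and label the result exploratory and non-randomised. The cost is the untestable assumption that attenders of the two programmes are comparable, and a smaller BAT group.

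Both use attendance data that the plan already provides for, so the extra work is limited to analysis.

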Therefore, we propose a proof-of-concept, single-blind RCT to primarily examine the efficacy of a 12-month, twice-weekly PRT program to improve cognitive function and reduce WMH progression in community-dwelling adults with SIVCI. The secondary objective is to assess the effect of PRT on regional brain volumes, white matter integrity, myelin content, functional connectivity, specific cognitive processes, physical performance, cardiometabolic risk factors, sleep, physical activity, mood, quality of life, blood biomarkers, and cortisol from saliva. The tertiary objective is to explore the underlying mechanisms by which PRT may promote cognitive function.

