##### Blood and saliva samples

In a subset of participants who consent, fasting blood samples will be collected in the morning by standard venipuncture at baseline, 6, and 12 months. Blood will be processed and stored at – 80 °C as plasma, serum, and whole blood. The main analytes of interest include pro and mature BDNF, IGF-1, VEGF, Cathepsin-B, irisin, adiponectin, sex steroid hormones (estradiol, estrone, testosterone), s100-B, and pro- and anti-inflammatory cytokines (e.g., IFN-γ, IL-1β, IL-4, IL-6, IL-10, IL-12p70, IL-13, IL-17, TNF-α, Rantes, CXCL1, IL-18, TGF-β). To examine potential genetic moderation of exercise efficacy, we will examine the BDNF Val66Met polymorphism, a common single-nucleotide polymorphism within the pro-domain region of the human BDNF gene resulting in an amino acid substitution of valine (Val) to methionine (Met) at position 66. We will also obtain the apolipoprotein E genotype. DNA will be extracted from whole blood by standard protocol and genotype will be determined by a TaqMan by-design assay. Remaining blood samples will be stored for future analyses.

In a subset of participants who consent, saliva samples will be taken to assess hypothalamic–pituitary–adrenal axis activity. Specifically, we will examine: (1) total cortisol concentration over the day (area under the curve); (2) cortisol awakening response, a distinct aspect of the circadian cortisol profile; and (3) changes in cortisol response to engaging in an exercise class with time of day held constant. Free cortisol levels will be assessed in salivary samples (Salivette®) collected 5× each day (at awakening, 30 min after awakening, 2 pm, 4 pm, and bedtime) for 2 consecutive days at each measurement point. Also, salivary samples will be collected immediately before and immediately after the first exercise class and the last exercise class to examine cortisol response to exercise.

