## Discussion

Although previous research has highlighted the benefit of aerobic training for people with SIVCI [25], further research is required to determine the effect of resistance training in this population. Consequently, the findings from this RCT will provide important insight into the efficacy of resistance training on improving cognitive function and slowing WMH progression in adults with SIVCI. In addition, our findings will provide greater understanding of the underlying mechanisms by which PRT promotes cognitive function in SIVCI.

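### The exploratory mechanism objective rests on a change-change association that gives randomised group no stated role and is not joined to the planned between-group effects, so on its own it cannot support statements about how PRT works

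*Protocol article*

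**What the plan says.** The Introduction separates two aims. The secondary objective is the effect of PRT on imaging, cardiometabolic, blood, saliva and other measures. The tertiary one is different: "The tertiary objective is to explore the underlying mechanisms by which PRT may promote cognitive function".

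For the tertiary aim, Statistical analyses gives a single sentence: "To explore underlying mechanisms, we will assess the association between changes in cognitive function with changes in: (1) neuroimaging outcomes; (2) cardiometabolic risk factors", with blood and saliva biomarkers as the third and fourth families. It mentions no group term, interaction or indirect effect.

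For the secondary aim, the same section applies the between-group mixed model: "Primary and secondary outcomes will be analyzed using this same analytic model". The PRT effect on each candidate will therefore be estimated. Nothing links that estimate to the mechanism analysis.

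The Discussion states what is expected: "our findings will provide greater understanding of the underlying mechanisms by which PRT promotes cognitive function in SIVCI". Its Public health subsection says much the same in more tentative words.

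On timing, Blood and saliva samples says "fasting blood samples will be collected in the morning by standard venipuncture at baseline, 6, and 12 months", in a consenting subset whose size is not given, and places saliva sampling at every measurement point. Brain MRI is at baseline and 12 months only (White matter hyperintensity quantification). The Cardiometabolic risk factors section gives no timing of its own. Design gives three measurement points for the trial as a whole.

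**The concern.** To call something a mechanism of PRT, two things are needed: PRT must move the candidate, and that movement must account for some of the effect on cognition. A correlation between two changes addresses neither. It asks whether people whose candidate changed more also changed more in cognition, whatever the cause.

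The protocol gives reason to expect such correlation without PRT. It treats vascular risk factors as drivers of SIVCI (Introduction) and WMH progression as a surrogate marker in this disease (Sample size calculation). A participant whose disease advances faster may worsen on several of these together. Changes taken over the same interval also do not show which moved first.

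What is at stake is the reading of a tertiary result: an association that may reflect only the course of the disease could be offered as insight into how PRT acts.

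**Working it through.** The protocol gives no figure for the mechanism analysis, so there is none to reproduce. The question is how often the named association would be positive if PRT did nothing.

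**Inputs**
- Completers: 35 per group, 70 in total (Sample size calculation). The inflation reproduces: 35 / (1 − 0.20) = 43.75, rounded up to 44 per group, 88 in all.
- Two-sided alpha 0.05.
- Correlation r between the two changes in the natural course: not given. Assumed 0, 0.2, 0.3 and 0.4.
- Size of the biomarker subset: not given. Assumed 40 for illustration.

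**Step 1. Association with no PRT effect on either variable.** By Fisher's z, the chance of p < 0.05 is approximately Φ(atanh(r) × √(n − 3) − 1.96). For n = 70, √67 = 8.185.
- r = 0.2: 0.2027 × 8.185 = 1.66; Φ(−0.30) = 0.38
- r = 0.3: 0.3095 × 8.185 = 2.53; Φ(0.57) = 0.72
- r = 0.4: 0.4236 × 8.185 = 3.47; Φ(1.51) = 0.93

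Simulation of 20,000 trials per setting agrees:

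| n | r = 0 | r = 0.2 | r = 0.3 | r = 0.4 |
|---|---|---|---|---|
| 70 | 5% | 39% | 72% | 94% |
| 88 | 5% | 46% | 81% | 97% |
| 40 (assumed subset) | 5% | 24% | 48% | 74% |

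Repeat runs differ by about one percentage point.

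**Step 2. Does adjusting for group help?** Hardly. Removing the arm means before correlating gives about 38%, 71% and 93% at n = 70, because the natural co-variation sits within each arm.

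**Step 3. Join the association to the randomised effect on the candidate.** If PRT does not move the candidate, the between-group test is positive in 5% of trials. Requiring both gives roughly 0.05 × 0.39 = 2.0%, 0.05 × 0.72 = 3.6% and 0.05 × 0.94 = 4.7%. Simulated values at n = 70 are 1.7%, 3.2% and 4.8%.

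**Step 4. What joining does not cure.** Suppose PRT does move the candidate by d = 0.6 (assumed), but the candidate has no causal effect on cognition. A two-sided t-test with 35 per group has power 0.70 at that effect. Requiring both conditions then gives about 0.70 × 0.38 = 27%, 0.70 × 0.72 = 50% and 0.70 × 0.93 = 65%. Simulation gives about 26%, 49% and 65%. The candidate-to-cognition path is not randomised, and shared disease course confounds it as before.

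The power of 0.70 in step 4 differs from the 0.80 stated in Sample size calculation. That is a separate matter and does not affect this point.

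**The case against.** The strongest reply has four parts.

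*The randomised comparison is already planned.* This stands. A reader might infer that the trial examines the candidates by correlation alone. The text does not support that, since Statistical analyses covers secondary outcomes with the between-group model. What is missing is the link between the two analyses.

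*The aim is exploratory, and the article is condensed.* Also fair. The objective is tertiary and worded as exploration, the text sets no significance rule for declaring a mechanism, and a fuller analysis plan may add model detail. A reader might infer that a significant correlation will be reported as a proven mechanism; that is a prediction, not something the article says. What remains is that the article names a method for this aim, and that method does not answer the aim's question even as exploration. Whether the association is pooled or adjusted for group is not stated, but step 2 shows that it matters little.

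*The percentages are not error rates.* Correct. They are the power to detect a correlation that was assumed to be real. They show that a positive result need not involve PRT. They do not show that the plan makes false claims at that frequency. At r = 0 the rate is the nominal 5%. The protocol gives no co-change figure, least of all for cytokines or cortisol.

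*Mediation analysis has its own confounding.* True, as step 4 shows. A reader might infer that a supported indirect effect would establish a mechanism. It would not, and the fix has to say so.

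**Conclusion.** The point holds as a cheap improvement to an exploratory analysis. The method named for the mechanism objective gives randomised group no stated role and is not connected to the between-group effects planned in the same section. It can be positive when PRT moves neither variable: about 39%, 72% and 94% of trials at n = 70 for r = 0.2, 0.3 and 0.4. If an effect of PRT on the candidate is also required, this falls to at most about 5%. Taken alone, the association cannot support the Discussion's statements about how PRT acts.

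The sizes rest on assumed correlations, normally distributed changes and 70 completers. The reasoning does not depend on them: a change-change association does not separate an effect of PRT from the course of the disease. The primary and secondary analyses are untouched.

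**What to change.** Make the mechanism analysis an exploratory mediation analysis that uses randomised group:

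1. Take the planned PRT-BAT effect on each candidate, adjusted for its baseline.
2. Estimate the association of the candidate with cognition, adjusted for group, baseline candidate and baseline cognition.
3. Report the indirect effect with an interval, for example by bootstrap.
4. Where a 6-month candidate value exists, relate it to 12-month cognition and adjust also for 6-month cognition, so that the candidate does not merely track cognition at the same visit. Six-month values are stated for blood and saliva. For cardiometabolic measures, confirm the timing first.
5. For MRI candidates, include group and state that temporal order cannot be shown.
6. State that the candidate-to-cognition path is not randomised and rests on no unmeasured confounding. Describe a supported indirect effect as consistent with a mechanism, not as proof. Report a candidate with no PRT effect as an association only, and word the Discussion to match.

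The cost is some analysis-plan wording and modest analysis time on data already to be collected. The downside is wider intervals, particularly in the biomarker subset, and fewer candidates described as possible mechanisms.
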